## 3. *Sample Size*

The sample size is influenced by the minimal desirable detectable effect of the intervention, the event rate of the outcome, and the duration of the intervention. The desired detectable effect is influenced by the magnitude of the plausible effect size and the importance of the preventable event. Initial estimates of a plausible effect size of multi-micronutrient supplementation on maternal mortality can be guided by childhood

mortality-related effects observed for other micronutrients such as vitamin A and iodine, which range from 20-70%. While acknowledging that physiological differences between children and pregnant women limit the utility of such information, additional perspective is gained from the results of the NNIPS-2 study which described a vitamin A-mediated 40% reduction in mortality related to pregnancy. Given the relatively low-cost of a prenatal nutrient-based intervention, the documentation of a 20-30% effect, especially under programmatic settings, would be important. The estimates of the maternal mortality ratio in various districts on Lombok range from 400 to 800 maternal deaths per 100,000 live births. For this intervention the unit of randomization will not be the individual woman, but the area or cluster of communities administered by the midwife. This improves logistical feasibility but reduces statistical power due to the potentially correlated outcomes within each cluster. Given the estimated between-cluster variability in MMR, we have calculated that a 20% increase in sample size is needed to compensate for the loss of statistical power from the cluster-based randomization. We further anticipate a loss to follow-up of approximately 10%. Lastly, because not all pregnancies result in a live birth, it is estimated that the required sample size be increased an additional 15% to compensate for abortions, miscarriage, and stillbirths. Given these factors, the sample size table below presents the number of pregnancies required to obtain significance for various observed reductions in MMR for the proposed 2-arm design.

| Detectable
reduction
(%) | Total pregnancies needed by baseline MMR
(deaths/100,000 live births) |                |                |
|-----------------------------------------|----------------------------------------------------------------------------------|----------------|----------------|

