|                                         | MMR=400                                                                   | MMR=600 | MMR=800 |
| 15                                      | 509,635                                                                          | 339,137        | 253,887        |
| 20                                      | 281,023                                                                          | 187,017        | 140,012        |
| 25                                      | 176,230                                                                          | 117,290        | 87,815         |
| 30                                      | 119,865                                                                          | 79,777         | 59,731         |
| 35                                      | 86,232                                                                           | 57,381         | 42,967         |
| 40                                      | 64,581                                                                           | 43,035         | 32,192         |

Assuming a conservative MMR estimate of 400 per 100,000 live births, enrollment of 120,000 pregnancies will allow determination of a reduction in MMR of at least 30% with a power of 80% and significance level of 0.05. Similar reductions in MMRT will also be detectable because such rates are expected to be higher given that deaths prior to a live-birth delivery would be included. Given the estimated 72,000 pregnancies per year in the 300 villages on Lombok, and taking into account the phased in implementation schedule, the SUMMIT activity will plan to enroll 126,000 pregnancies over a 2 year active recruitment period. If MMR and MMRT approach 600-800 per 100,000 live births or pregnancies, which is possible considering the high rates of infant and under-five mortality, the sample size of 126,000 pregnancies will allow determination of a statistically significant reduction in MMR and also MMRT of 22-25%.

For infant mortality it will be important to also determine the age-specific effects on neonatal mortality rate (NMR, birth to 30 day mortality) and post-neonatal mortality rate

(PNMR, 1 to 12 months). The projected sample size and trial duration will allow detection of at least a 10% change in NMR and PNMR. In addition, the study will easily detect a difference of 10% in the proportion of low-birth weight (LBW) infants.

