| Detectable
reduction
(%) | Total live births (LB) needed |                        |                      |
|-----------------------------------------|--------------------------------------|------------------------|----------------------|
|                                         | NMR=46/1000 LB                | PNMR=64/1000 LB | LBW=15/100 LB |
| 10                                      | 83,012                               | 58,613                 | 22,862               |
| 15                                      | 36,231                               | 25,597                 | 10,016               |
| 20                                      | 20,006                               | 14,142                 | 5,552                |
| 25                                      | 12,561                               | 8,899                  | 3,498                |

As is general practice for community-based trials, a Data Safety and Monitoring Committee will be convened, and trial data will be evaluated after two years. Should documentable reductions be likely, the committee will decide whether the trial should be terminated or extended. For example, if a 20% reduction in MMR is observed in the multi-nutrient group compared to a MMR of 600/100,000 live births in the iron/folate arm, an approximate 6-month extension would be needed to demonstrate statistical significance.

Sample size determinations are needed for the evaluation of the impact of activities, such as promotion of prenatal care and nutrition, accompanying the supplement distribution. Through the baseline demographic surveillance and continued monitoring of maternal and infant mortality as the intervention is phased in, we propose to document the effect of the activities associated with program implementation on maternal and infant mortality. This will be estimated by comparing MMR, MMRT, and IMR between the non-intervention areas and the iron/folate arm of the intervention area. For the non-intervention area we estimate that maternal and infant mortality rates will be estimated for 54,000 pregnancies. This will be compared to the rate obtained for the iron/folate arm of the intervention for 63,000 pregnancies. This will enable detection of at least a 20-25% (power=80% with  $p<0.05$ ) effect of the program implementation, independent of the multi-micronutrient impact.

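### The monitoring committee's worked example understates the extension (6 months against about 10 from the protocol's own table), and the terminate-or-extend rule names no test level other than 0.05

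*Protocol*

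**What the plan says.** All the relevant text is in protocol section VIII.B.3, Sample Size.

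- **The table.** The text introducing the MMR table says that it "presents the number of pregnancies required to obtain significance for various observed reductions in MMR". The first column, however, is headed as detectable reduction, and the paragraph after the table reads the 30% row at MMR 400 as what 120,000 pregnancies can detect "with a power of 80% and significance level of 0.05".
- **Enrolment.** "the SUMMIT activity will plan to enroll 126,000 pregnancies over a 2 year active recruitment period". Section VIII.B.1 puts annual pregnancies in the 300 villages at 72,000.
- **The look.** Trial data are evaluated after two years. "Should documentable reductions be likely, the committee will decide whether the trial should be terminated or extended".
- **The example.** The illustration is: "if a 20% reduction in MMR is observed in the multi-nutrient group compared to a MMR of 600/100,000 live births in the iron/folate arm", then "an approximate 6-month extension would be needed to demonstrate statistical significance".

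The protocol gives no separate significance level for the two-year evaluation.

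**The concern.** The example is the only guidance the committee gets on how long an extension should be, and it appears to conflict with the table a page earlier. A power table gives the sample size at which a *true* reduction will be found significant in 80% of trials. It does not give the size at which an *observed* reduction becomes significant, which is much smaller. The introductory text calls the table one of observed reductions, and the example carries that confusion into the committee's instructions.

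The second issue is the decision itself. The text sets out the trigger (likely reductions), the options (terminate or extend) and, through the example, both the input (the difference seen between arms) and the aim (reaching significance). With 0.05 as the only level in sight, a reader could apply it at two years and again after an extension. Maternal mortality is the lead outcome, so both the length of the trial and the error rate of its main claim are affected.

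**Working it through.** **1. Reproduce the table cell (20%, MMR 600).** Inputs: p1 = 0.0060, p2 = 0.0048, two-sided 0.05, power 80%, 20% for clustering ("a 20% increase in sample size is needed to compensate for the loss of statistical power from the cluster-based randomization"), 10% loss and 15% of pregnancies without a live birth.

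- n per arm = [1.96√(2p̄q̄) + 0.842√(p1q1 + p2q2)]² / (p1 − p2)², with p̄ = 0.0054, gives 58,548.
- With the Fleiss continuity correction: 60,203.
- Total = 2 × 60,203 × 1.2 × 1.1 / 0.85 ≈ 186,980, against 187,017 in the table.

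The table is therefore an 80%-power table for true reductions. A one-sided test would need about 147,300 and does not fit.

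**2. Check the 126,000.** Monthly accrual is 72,000/12 = 6,000. Phase-in by thirds over three-month steps gives 6,000 + 12,000 + 18 × 6,000 = 126,000 at 24 months.

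**3. Extension on the power reading.** (187,017 − 126,000)/6,000 = 61,017/6,000 = 10.2 months. Six months gives 126,000 + 36,000 = 162,000.

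Power = Φ{[(p1 − p2)√n − 1.96√(2p̄q̄)] / √(p1q1 + p2q2)}, with n per arm scaled from the table as N × 58,548/187,017:

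| Pregnancies | Power, true 20% reduction |
|---|---|
| 126,000 | 63% |
| 162,000 | 74% |
| 187,017 | 80% |

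**4. Extension on the literal reading (20% is the observed reduction).**

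- Live births per arm with complete outcomes: 126,000 × 0.85 × 0.90 / 2 = 48,195.
- Deaths: 48,195 × 0.0060 ≈ 289 and 48,195 × 0.0048 ≈ 231.
- z = 0.0012/√(2 × 0.0054 × 0.9946/48,195) = 2.54. Dividing by √1.2 for clustering gives 2.32, p = 0.020. With the table's full inflation, z = 2.30 and p = 0.021.
- An observed 20% reaches z = 1.96 at about 187,017 × (1.96/2.80)² ≈ 91,500 pregnancies.

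So no further enrolment is needed on this reading.

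**5. Where 6 months might come from (conjecture).** Converting the requirement to live births (187,017 × 0.85 = 158,964, or 187,017/1.15 = 162,623) and subtracting 126,000 *pregnancies* gives 5.5 to 6.1 months. That would be a mismatch of units. The protocol does not show its calculation.

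**6. Type I error.** Let Z1 be the statistic at the look and Z2 the statistic after extension, with correlation √t and t the information fraction. If 0.05 applies at both points and the trial is extended only when Z1 > 0:

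α = P(|Z1| > 1.96) + P(0 < Z1 ≤ 1.96 and |Z2| > 1.96).

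For t = 126/162 = 0.778 this is 0.050 + 0.011 = 0.061.

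| Rule | 126,000 then 162,000 | 126,000 then 187,017 | Look with 69% of outcomes mature (assumed), then 162,000 |
|---|---|---|---|
| 0.05 twice, extend if Z1 > 0 | 6.1% | 6.3% | 6.6% |
| 0.05 twice, extend if Z1 > 1 | 6.0% | 6.2% | 6.2% |
| 0.05 twice, extend if Z1 > 1.5 | 5.7% | 5.7% | 5.6% |
| 0.05 twice, extend every non-significant trial | 7.2% | 7.7% | 8.2% |
| Extend if Z1 > 1 and then test once, at the end | 4.9% | 4.8% | 4.6% |

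**The case against.** **The example is only an illustration.** It is marked as an example and as approximate, and the planned size rests on 30% at MMR 400, not on this scenario. That is true, and the sample size is untouched. But it is the only figure offered for an extension, and it is 4 months short of the adjoining table.

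**Outcomes will be incomplete at two years.** If 69% were mature (an assumption; the protocol gives no figure), the observed 20% would give z = 2.32 × √0.69 = 1.93, p = 0.054, so more data would be needed after the look. This stands. Those data, however, come from women already enrolled, whose follow-up to three months after delivery is already planned in Phase II. The literal reading still does not produce a 6-month extension of enrolment.

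**The word observed is a slip.** The column heading and the stated 80% power show what was meant. That is fair for the table alone. The slip matters because the example repeats it.

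**The rule is less rigid than it can be made to sound.** A reader might infer that the trial is extended repeatedly until significant, with 0.05 applied each time. The text describes one evaluation and a discretionary decision, and does not say that significance is claimed at the look. Boundaries may also sit in an analysis plan or committee charter that is not shown, so their absence here is not itself a fault. Likewise, the 7% to 8% figures require extending trials that trend against multi-micronutrients, whereas the text speaks of extension only when reductions are likely.

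**Timing.** One might infer that a look at the end of recruitment comes too late to act on. The protocol does not support this: at 6,000 enrolments a month and the average 6-month supplementation period in section VIII.B.11, about 36,000 women would still be taking supplements.

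**Conclusion.** The extension figure is wrong on the protocol's own numbers. About 10 months, not 6, is needed to reach 80% power for a true 20% reduction at MMR 600; 6 months gives about 74%. Taken as an observed reduction, 20% with complete outcomes on 126,000 is already at p of about 0.02. These results rest only on the protocol's table, enrolment target, accrual rate and inflation factors.

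The error-rate part is conditional. If significance may be claimed at 0.05 at the look or after a favourable-trend extension, two-sided type I error is about 6.1% to 6.6%, and somewhat lower with a stricter trigger. A single final test does not inflate it. The documents therefore do not support a flat statement that the false-positive rate exceeds 5% as written. They do support the narrower point that the protocol fixes an extension driven by the observed arm difference and aimed at significance, without saying which of these tests applies.

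This should be corrected, but it does not undermine the planned sample size.

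**What to change.** 1. **Example.** Replace 6 months with about 10 months of further enrolment, stated as what 80% power requires for a *true* 20% reduction at MMR 600.
2. **Table description.** Describe the table as true reductions detectable with 80% power, and remove the reference to observed reductions needed for significance.
3. **Two-year look.** State a strict efficacy boundary, for example Haybittle-Peto at p < 0.001, with the final test at about 0.05.
4. **Extension.** State that any extension is decided on the pooled, blinded count of maternal deaths or, if the committee may use the arm difference, that the final analysis uses a prespecified combination test.

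The cost is a change of wording in the protocol and the committee's charter. A Haybittle-Peto boundary costs almost no power. The real downside is that a promising unblinded difference could no longer lead to an unadjusted extension. The sponsor would also have to plan for an extension about 4 months longer than the text now suggests.

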*Sample Size:* The SUMMIT activity will aim to detect a reduction in both MMR and MMRT of at least 30% with a power of 80% and significance level of 0.05. Current estimates of the MMR in various districts on Lombok range from 400 to 800 maternal deaths per 100,000 live births and randomization for the trial will be by clusters consisting of geographic areas serviced by each of the 300 midwives providing prenatal care. Assuming 400 maternal deaths per 100,000 live births and a 10% loss to follow-up, the trial would require enrollment of 102,000 live birth pregnancies allocated to either an iron/folate or multinutrient supplement to detect a 30% reduction in MMR. Because not all pregnancies result in a live birth, it is estimated that the required sample size be increased an additional 15% to 120,000. This sample size will also allow detection of similar reductions in MMRT. It is proposed that enrollment be phased in over a 6-month period and continue for at least 2 years to accommodate seasonal effects. The phased in implementation along with the approximately 72,000 pregnancies occurring each year throughout the trial area yields a projected enrollment of 126,000 pregnancies. The additional margin of enrollment provides the ability to detect reductions in MMR as little as 22% if ratios approach 800 per 100,000 live births. With regard to low birth weight and infant mortality rates, the projected sample size will allow detection of at least a 10% reduction in low birth weight and infant mortality rates, including neonatal mortality rates. Equally important is determination of the impact of the social marketing and education programs that will accompany the trial implementation in the intervention area. Data concerning outcome variables in the absence of the intervention will be collected during the phase-in period prior to enrollment. This will result in the ability to detect at least a 25% difference in MMR between the iron/folate arm of the intervention area compared non-intervention areas.

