The largest city on Lombok is Mataram, the capital of NTB province, with a population of approximately 300,000. West Lombok district consists of 13 sub districts and 99 villages with a population of around 530,000 people. Central Lombok consists of 12 sub districts and 119 villages and has a population of about 750,000 people. East Lombok consists of 16 sub districts and 109 villages with a population of about 1,000,000 people. The trial will be conducted in approximately 300 villages in West, Central and East Lombok Districts. Based on demographic data from the government of NTB and additional data collected from NGOs, we estimate that 72,000 pregnancies will occur annually in the 300 villages.

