## 2. *Design and Methods*

The proposed SUMMIT activity is a double blind, community-based, cluster-randomized, controlled intervention designed to assess the relative impact of multi-micronutrient supplements compared to iron/folate supplements on maternal mortality, infant mortality and low birth weight. Pregnant women will be randomized to one of approximately 300 clusters defined by the geographic area serviced by a trained midwife. This means that all women attended by a particular midwife will receive the same type of supplement. Clustered randomization was chosen due to the logistical and scientific difficulties associated with individual randomization in large scale longitudinal trials. Pregnant woman will be provided with either a daily multi-micronutrient supplement containing iron, folate, vitamin A, and zinc, along with additional B vitamins, minerals, anti-oxidants (for precise composition, see Appendix 3a), or an identical-looking daily supplement containing 30 mg iron and 400 µg folate. There will be no blank placebo group because iron/folate supplementation distribution to pregnant women is the current policy of the GOI.

The intervention will be preceded by a 6-month baseline demographic surveillance period to estimate area-specific maternal and infant mortality rates. Supplementation will then be phased in step-wise by implementation in 1/3 of the villages over 3 successive 3-month intervals. Women who refuse to be included in the trial and those in the pre-intervention areas will receive the standard GOI iron/folate tablets. The GOI iron/folate tablets will, therefore, not be withdrawn from the island but will only be used for individuals not enrolled in the intervention portion of the activity.

Supplements will be provided free to all women with a confirmed pregnancy, from the first antenatal consultation up to three months postpartum. As a joint activity between HKI and the GOI, the existing government system will distribute the supplements to pregnant women and the government-trained midwives will be involved in monitoring the health impact. HKI project staff will also encourage the midwives to provide maximum supplementation coverage. Additional non-invasive surveillance will be carried out by HKI project staff to allow adequate assessment of compliance and health impact.

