## *12. Data management and analysis*

The first check of the forms will be performed in the field by the field supervisors. Data entry will be done using the *SPSS for Windows* program. Data will be entered in batches, and 10% of each batch will be cross-checked by data-entry supervisors. Batches for which unacceptable error rates are obtained will be re-entered and checked until acceptable

quality standards are met. The data-entry program will prohibit entry of invalid or impossible values and generate a query for follow-up. After data have been entered, additional outliers will be identified and checked against the original questionnaires. Queries regarding unclear or incomplete data will be referred to the field for appropriate follow-up. This system has been field-tested by the HKI NSS and functions well. Primary analyses will compare key outcome event rates event rates, MMR, MMRT, PNMR, and LBW in the multi-micronutrient group with the iron/folate group. However, the SUMMIT activity will not only provide information concerning the impact of micronutrients on these indicators, but it will also assess the specific impact of activities accompanying the intervention such as promotion of prenatal care and social marketing. This will be done by comparison of event rates in the pre and post-intervention areas for the iron/folate arm. This enables one to individually assess the impact of the various components of the SUMMIT activity on the key health outcomes. Relative cost-benefit analyses can therefore be carried out for the various interventions.

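### The programme-effect contrast is stated as overall rate against overall rate, yet the phase-in gives its two sides different mixes of areas (about 22/33/44% against 38/33/29%), so mortality differences between areas can pass for a programme effect

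*Protocol*

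**What the plan says.** Two places in the Protocol describe how the effect of promotion, education and strengthened care will be separated from that of the supplement. Section VIII.B.3 (Sample Size) says "This will be estimated by comparing MMR, MMRT, and IMR between the non-intervention areas and the iron/folate arm of the intervention area", and sets an estimated 54,000 non-intervention pregnancies against 63,000 in the iron/folate arm, with a detectable effect of 20-25% at 80% power. Section VIII.B.12 (Data management and analysis) says "This will be done by comparison of event rates in the pre and post-intervention areas for the iron/folate arm". Neither mentions stratification, weighting or adjustment by area.

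The non-intervention experience comes from the period before each village starts. Section VIII.B.2 (Design and Methods) says "The intervention will be preceded by a 6-month baseline demographic surveillance period to estimate area-specific maternal and infant mortality rates" and "Supplementation will then be phased in step-wise by implementation in 1/3 of the villages over 3 successive 3-month intervals". The Executive Summary adds "It is proposed that enrollment be phased in over a 6-month period and continue for at least 2 years to accommodate seasonal effects".

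On differences between areas, section VIII.B.3 says "The estimates of the maternal mortality ratio in various districts on Lombok range from 400 to 800 maternal deaths per 100,000 live births", and section VIII.B.4 expects substantial heterogeneity between three climatic zones. Section VIII.B.6 randomises the supplement code to midwives. No section says how villages are assigned to the three phase-in steps.

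**The concern.** In a step-wise roll-out, a village that starts late adds more time to the non-intervention side and less to the trial side. A village that starts early does the opposite. One overall rate on each side then compares different mixes of places. If late-starting areas have higher mortality than early-starting ones, the programme looks beneficial when it does nothing. If they have lower mortality, a real benefit is masked.

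This arises from where the pregnancies occur. It would remain with no time trend and with identical detection of deaths. The Executive Summary calls this evaluation equally important, and section V makes it the basis of a cost-benefit analysis meant to guide government health budgets.

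**Working it through.** **Inputs.** From section VIII.B.1: "we estimate that 72,000 pregnancies will occur annually in the 300 villages". From section VIII.B.2: 6 months of baseline, then thirds of the villages in 3-month steps. From section VIII.B.3: "the SUMMIT activity will plan to enroll 126,000 pregnancies over a 2 year active recruitment period", and a 20% inflation for clustering. Assumptions: the thirds have equal numbers of pregnancies, half of each third is iron/folate, and the live-birth proportion is constant.

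**1. Reproduce the plan's totals.** 72,000 / 12 / 3 = 2,000 pregnancies a month per third. With starts at months 0, 3 and 6:

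| Third | Non-intervention months | Comparator | Enrolment months | Enrolled | Iron/folate half |
|---|---|---|---|---|---|
| First | 6 | 12,000 | 24 | 48,000 | 24,000 |
| Second | 9 | 18,000 | 21 | 42,000 | 21,000 |
| Last | 12 | 24,000 | 18 | 36,000 | 18,000 |
| Total | | 54,000 | | 126,000 | 63,000 |

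All three totals match the protocol. Starts at mid-interval give 63,000 and 117,000, and starts at months 3, 6 and 9 give 72,000 and 108,000, so neither fits.

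**2. Area shares.** Comparator: 12/54, 18/54, 24/54 = 22.2%, 33.3%, 44.4%. Iron/folate arm: 24/63, 21/63, 18/63 = 38.1%, 33.3%, 28.6%.

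**3. Apparent effect when the true effect is zero.** Each overall rate is the sum of share × MMR. The MMRs by third are assumed, within the protocol's 400-800 range.

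| MMR first/second/last | Comparator | Iron/folate | Apparent change |
|---|---|---|---|
| 550/600/650 | 611 | 595 | -2.6% |
| 500/600/700 | 622 | 590 | -5.1% |
| 400/600/800 | 644 | 581 | -9.9% |
| 800/600/400 | 556 | 619 | +11.4% |

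For example, 0.222×400 + 0.333×600 + 0.444×800 = 644, 0.381×400 + 0.333×600 + 0.286×800 = 581, and 581/644 = 0.901.

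**4. If villages are spread at random over the thirds.** Clusters average 126,000/300 = 420 pregnancies. A design effect of 1.2 implies an intracluster correlation of 0.2/419 = 0.00048. At MMR 600 the between-cluster SD is √(0.00048 × 0.006 × 0.994) = 0.00169, or 28% of the mean. With 100 clusters per third and a share difference of 0.444 - 0.286 = 0.159, the SD of the distortion is 0.159 × √2 × 0.28/√100 = 0.6%. At MMR 400 it is 0.8%.

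**5. Consequence at the extreme.** Take live births as 0.85 × pregnancies, divided by 1.2 (clustering) and 1.10 (loss): 34,773 against 40,568. At 400/600/800 with no true effect, a two-sided 5% test rejects about 20% of the time. At 800/600/400, a true 25% reduction gives 619 × 0.75 = 464 against 556, an apparent 16%. Power is then about 42%, compared with 81% at a uniform 600.

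**6. Cost of stratifying.** At a common rate, the variance is proportional to 1/W, where W is the sum over strata of c×t/(c+t), with c and t the comparator and iron/folate pregnancies (thousands).
- Crude: 54×63/117 = 29.08.
- By third: 12×24/36 + 18×21/39 + 24×18/42 = 8.00 + 9.69 + 10.29 = 27.98. Variance ratio 29.08/27.98 = 1.04.
- By village: only iron/folate villages contribute, so the comparator halves to 6/9/12. W = 6×24/30 + 9×21/30 + 12×18/30 = 4.8 + 6.3 + 7.2 = 18.3. Variance ratio 29.08/18.3 = 1.59.

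**The case against.** The strongest reply is that the protocol fixes no estimator. Section VIII.B.3 is a sample-size passage, section VIII.B.12 is equally brief about the primary comparison, and area adjustment is ordinary content for an analysis plan that is not shown. Section V links this evaluation to district-specific rates, and the baseline is meant to give area-specific ones. This stands in part: stratified analysis is not ruled out, and the data would support it. But the contrast that is stated, and powered at 54,000 against 63,000, sets overall rates side by side. Reading section VIII.B.12 as before-and-after in the iron/folate villages does not help. That comparator would be 27,000, and its shares (6/27, 9/27, 12/27) would still be 22/33/44%.

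The second reply is that the large figures are a worst case, and this stands. District MMRs are not firmly established. Thirds at 400/600/800 have a variance of 163² against the 169² implied between clusters in step 4. They would absorb about 94% of it (about 80% at 357 live births per cluster, 420 × 0.85), leaving little variation between villages within a third.

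A reader might infer roll-out district by district, since the three districts have 99, 119 and 109 villages. The protocol does not say so, and the populations (about 530,000, 750,000 and 1,000,000) do not make equal thirds. Splitting pregnancies by population gives a comparator of 50,289 to 57,711 depending on district order, and no order returns 54,000.

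**Conclusion.** The point holds as a weakness in a stated supporting contrast. The unequal shares follow from the protocol's own totals, given equal thirds and starts at months 0, 3 and 6. Nothing stated makes the thirds alike. The resulting distortion has unknown size and direction: an SD of 0.6-0.8% under random spread, about 5% at 500/600/700, and about 10-11% at the illustrative extreme, which is roughly half of the 20-25% target.

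Three stronger conclusions are not supported. The documents do not show that a bias near 10% will occur. The multi-micronutrient versus iron/folate comparison is not affected, because both arms run concurrently under a randomised supplement code. Nor would stratifying by area make the programme contrast unconfounded: non-intervention experience falls in months 0-12 from the start of surveillance and iron/folate enrolment in months 6-30, so calendar time remains a separate problem.

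**What to change.** In sections VIII.B.3 and VIII.B.12, state that the programme effect is estimated within phase-in third, or within zones or sub-districts that contain both supplement arms, and that the stratum estimates are combined (for example with Mantel-Haenszel weights). Stratifying by third removes the distortion between thirds when there is no true effect and costs about 4% more variance. It needs only the area and start date of each village.

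Do not stratify by village. Multi-micronutrient villages have no iron/folate pregnancies, so half the comparator would be lost and the variance would rise by about 59%.

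In section VIII.B.2, let the computer-generated randomisation already planned in section VIII.B.6 also assign phase-in order, balanced across climatic zones and supplement arms. The small cost is a less contiguous roll-out. This has to be settled before roll-out begins, because the order cannot be changed afterwards. Calendar time needs its own treatment in this contrast.
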